## Abstract

**Background:**

In older adults, multidomain training that includes physical and cognitive activities has been associated with improvement of physical and cognitive health. The goal of the multisite StayFitLonger study is to assess a home-based computerised training programme, which combines physical exercises, stimulating cognitive activities and virtual coaching.

**Methods:**

One hundred twenty-eight cognitively healthy older adults will be recruited from the community in Switzerland, Canada and Belgium. The study will comprise (1) a 26-week double-blind randomized controlled efficacy trial and (2) a 22-week pragmatic adherence sub-study. In the efficacy trial, participants will be randomly assigned to an experimental or an active control intervention. In the experimental intervention, participants will use the StayFitLonger programme, which is computerised on a tablet and provides content that combines physical activities with a focus on strength and balance, as well as divided attention, problem solving and memory training. Outcomes will be measured before and after 26 weeks of training. The primary efficacy outcome will be performance on the “Timed-Up & Go” test. Secondary outcomes will include measures of frailty, cognition, mood, fear of falling, quality of life, and activities of daily living. Age, sex, education, baseline cognition, expectation, and adherence will be used as moderators of efficacy. Following the 26-week efficacy trial, all participants will use the experimental programme meaning that participants in the control group will ‘cross over’ to receive the StayFitLonger programme for 22 weeks. Adherence will be measured in both groups based on dose, volume and frequency of use. In addition, participants’ perception of the programme and its functionalities will be characterised through usability, acceptability and user experience.

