##### Analysis of moderators

Age, sex, education and score on MoCA, four variables considered as time-invariant for the duration of the study, will be assessed as potential moderators of the impact of training on primary and secondary outcomes. Prior to their use, we will verify that they are independent from each other with a chi-squared test or correlations.

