#### Variables

*Adherence.* For the entire duration of the study (between T0 and T1, and T1 and T2), three measures of adherence in relation to the device usage will be recorded directly from the application (Table 3): dose measured by the time (min) spent on the programme per week; volume corresponding to the total number of repetitions performed per week within each activity (e.g., 3 quizzes completed while using the Quiz activity); and frequency corresponding to the number of sessions per week. These will be recorded separately for the physical and cognitive activities. Adherence will be calculated for each individual by plotting weekly data over the entire training period.

**Table 3 Tab3:** List of variables measured during the adherence sub-study

Adherence sub-study variables		Timepoints		
***Domain***	***Variable***	T0	T1	T2
Adherence	Dose variable: total time of training for each activity	During training		
	Volume variable: number of times each activity is carried out			
	Frequency variable: number of training sessions of at least 30 min performed per month			
User experience	Ad-hoc questionnaire exploring the quality of the introductory course	X		
	AttrakDiff 2 scale		X	X
Acceptability	Ad-hoc questionnaire to obtain ratings on different components (enjoyment, appropriateness, safety, self-evaluation)		X	X
Usability	Ad-hoc questionnaire exploring the impact of unique features of the programme (virtual coach, social interactions, preference, gamification, educative content, self-management, usability)			X

*User experience.* The AttrakDiff 2 scale [78] will evaluate user experience (Table 3) with a 28-item questionnaire given at T1 and T2. It will measure attractiveness, pragmatic quality and hedonic qualities (stimulation and identity) of the application. Pragmatic quality corresponds to usability for instance efficiency, effectiveness and learnability. Hedonic qualities refer to the programme’s originality and beauty. In addition, a 9-item questionnaire will be given at T0 to ask participants’ knowledge regarding the effects of cognitive and physical interventions and the quality of the introductory courses.

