#### Statistical analyses

Dose, frequency and volume variables will be analysed with polynomial regression models including linear and non-linear trajectories. This will allow to establish the best fitting model describing the use of the programme over time. Regression analyses will examine whether the cumulative values on adherence variables are predicted by personal characteristics, and the group to which they were assigned. We will also examine adherence dichotomously by classifying participants as a function of whether they maintain or not the recommended dose of the programme over time. Finally, we will evaluate whether change scores on primary and secondary measures of efficacy are correlated with adherence.

Qualitative analyses will be used to characterize usability, acceptability and user experience. In addition, correlations analyses between these parameters and a series of variables (age, sex, education, cognitive profile, participant’s technology and gaming profile) will be performed.

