We are aware of the potential limitations associated with this study. First, the StayFitLonger study spans over a full year and it is hard to predict whether participants will commit for such an extended period of time. Note, however, that we rely on a two-part design, with the RCT portion only lasting 26 weeks, and that attrition will be examined separately for the two portions. Second, while the use of feedback and rewards in the programme was meant to boost motivation, the frequency at which they appear has been set as a fixed parameter to avoid a bias between participants. Hence, this aspect was not personalized. In order to take into account that some participants may dislike receiving regular feedback, they will be able to deactivate this feature during the adherence sub-study. Adherence will be measured from the tablet application, but it is possible that some participants, intentionally or not, start an activity and let the application run in the background while they are actually not doing the activity. To counteract this possibility, the StayFitLonger programme includes a function that stops the application after 10 min of inactivity. However, it has not been implemented in the active control programme. This will be monitored as carefully as possible during data analysis to assess possible outliers in the time of use data of the active control group.

In conclusion, the StayFitLonger study will examine the efficacy, adherence and perception of a home-based computerised multi-modal training programme in robust and pre-frail older adults. Positive results on the StayFitLonger study will pave the way to further development and commercialisation of a scientifically grounded and empirically validated application which will improve the physical and cognitive health associated with independent life at home.

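### Adherence and expectation are called moderators in the abstract but not in the moderator section, and adherence, a post-randomisation measure whose dose is logged differently by arm, cannot serve as a moderator

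*Protocol article*

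**What the plan says.** **Moderators.** The abstract (Methods) lists six: "Age, sex, education, baseline cognition, expectation, and adherence will be used as moderators of efficacy". The section Analysis of moderators lists four: "Age, sex, education and score on MoCA, four variables considered as time-invariant for the duration of the study".

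**Adherence.** Under Adherence sub-study, Variables, "three measures of adherence in relation to the device usage will be recorded directly from the application", covering both T0 to T1 and T1 to T2. The measures are dose (time), volume (repetitions) and frequency (sessions); Table 3 counts a session towards frequency only if it lasts at least 30 minutes. The sub-study's Statistical analyses section models adherence as an outcome and then adds that "we will evaluate whether change scores on primary and secondary measures of efficacy are correlated with adherence".

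**Expectation.** Table 2 schedules the questionnaire at T0, T1 and T2. The Discussion plans a comparison between groups and a look at its relation to pre-post change.

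**Recording.** The limitations part of the Discussion says that "the StayFitLonger programme includes a function that stops the application after 10 min of inactivity". It continues: "However, it has not been implemented in the active control programme". The stated response is careful monitoring during data analysis "to assess possible outliers in the time of use data of the active control group".

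**Coach.** The StayFitLonger programme section gives improved adherence as a purpose of the virtual coach. The active control section says that arm has no coach.

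**The concern.** Two things are wrong together. First, a reader cannot tell which moderator tests are pre-specified: the abstract promises two that the section devoted to moderators does not contain. Second, one of those two is not a moderator in the usual sense. A moderator should be fixed before treatment starts, so that comparing arms within its levels is still a randomised comparison. Adherence is produced after allocation, and one arm contains a component designed to change it. Participants at a given level of adherence in one arm are therefore not comparable with those at the same level in the other.

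The measurement adds to this. Recorded control-arm minutes may include idle time that the StayFitLonger application would have cut. Even without idle time, a minute of strategy training and a minute of crosswords are different exposures.

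At stake is a reported dose-response, or its apparent absence or reversal, that reflects the arm difference, the logging rule or the participants' motivation and health. Adherence is one of the study's two major objectives and the authors foresee commercial development, so such a result would be read with interest.

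**Working it through.** **1. The lists side by side**

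| Variable | Abstract | Analysis of moderators | Elsewhere in the article |
|---|---|---|---|
| Age, sex, education | moderator | moderator | – |
| Baseline cognition (MoCA) | moderator | moderator | – |
| Expectation | moderator | absent | group comparison; relation to pre-post change (Discussion) |
| Adherence | moderator | absent | outcome; correlate of change scores (sub-study analyses) |

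That is 6 against 4. The two extra variables are the ones that can change during the study. Expectation has a baseline value and adherence has none. The abstract does not say which expectation value would be used.

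**2. Which adherence measures are exposed, T0 to T1**

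- Dose: directly, because idle minutes count in the control arm without limit.
- Frequency: where the 30-minute threshold of Table 3 applies, since idle time can carry a short session over it.
- Volume: little affected by idle time, but it counts unlike activities in the two arms.
- T1 to T2: everyone in the sub-study uses StayFitLonger, so the cut-off is the same for all.

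An outlier check catches extreme idle time. It does not remove moderate idle time spread over many control participants.

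**3. Illustration A: correlation pooled over arms, no dose effect in either arm**

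The plan states no figure on this point, so there is none to reproduce. Assume equal arms, unit within-arm SDs, improvement d SD greater in StayFitLonger, and recorded minutes a SD higher in control. Then

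r = −0.25·d·a / √[(1 + 0.25d²)(1 + 0.25a²)].

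For scale, 23.5 per group at 80% power and two-sided 0.05 (Sample size calculation, robust stratum) corresponds to d of about 0.84. The sub-study has about 96 participants; 25% dropout leaves 96 × 0.75 = 72. The value of a is an assumption with no source in the article.

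- d = 0.84, a = 1: r = −0.21 / √(1.1764 × 1.25) = −0.17. Fisher's z is 0.175 × √69 = 1.45 for n = 72 and 0.175 × √93 = 1.69 for n = 96. The probability of p < 0.05 is about 31% and 39%; simulation gives about 31% and 40 to 41%.
- d = 0.4, a = 0.5: r = −0.05 / √(1.04 × 1.0625) = −0.05. The probability is about 7% at either n.
- a = 0: r = 0, and the rate is the nominal 5%.

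If the coach raised StayFitLonger use enough to make a negative, the sign of r would reverse and a spurious positive dose-response would appear.

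**4. Illustration B: arm-by-adherence interaction**

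Setting: n = 96, no treatment effect, no causal effect of adherence, and latent health driving both adherence and change (loading 0.5 on each), 2,000 runs per setting. All of this is assumed.

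| Setting | Interaction significant | Shift in adherence-adjusted arm effect |
|---|---|---|
| Same recording in both arms | 4.3% | 0.00 SD |
| Idle time added in control only, mean 1 SD | 10.8% | 0.19 SD |
| Idle time added in control only, mean 2 SD | 23.4% | 0.30 SD |
| Same recording; health-adherence loading 0.7 in StayFitLonger, 0.3 in control | 17.1% | 0.00 SD |
| The same, plus idle time in control, mean 1 SD | 33.9% | 0.22 SD |

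The fourth row shows that equal logging would not be enough: a different link between health and adherence in the two arms produces false interactions by itself. In the first row, adherence and change still correlate at about 0.5 × 0.5 = 0.25 through health alone.

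**The case against.** The strongest reply is that all six variables have a place in the body of the article. The moderator section limits itself to time-invariant variables, adherence is taken up in the sub-study analyses, and expectation in the Discussion. On that view the abstract uses the word loosely, no arm-by-adherence interaction is specified anywhere, and the repair is a matter of wording. Much of this stands. A reader might infer that the article contradicts itself on whether adherence will be examined at all. It does not: adherence is related to change scores either way. What is unresolved is whether it will be tested as a moderator, which the abstract says it will.

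A reader might also infer that the planned correlation pools the arms. The article does not say so, and an article may leave that detail to the full plan. Nor does it show that control minutes will be higher: idle time pushes them up, while the coach pushes StayFitLonger use up and could offset or reverse the gap. The percentages for the pooled correlation are therefore conditional.

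The authors do disclose the missing cut-off and plan to monitor it, which deserves credit but deals only with extremes. Finally, within-arm analysis does not remove confounding by motivation and health, and there is no need to discard the control arm: reporting each arm separately removes the between-arm artefact equally well.

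**Conclusion.** The point holds in limited form. The moderator lists in the abstract and in the methods disagree by two variables and need reconciling. Adherence should not be one of the moderators, on the article's own facts: it is post-randomisation, it is targeted by a component of one arm only, it counts different activities by arm, and its dose (and frequency where the 30-minute threshold applies) is logged under different idle-time rules between T0 and T1.

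The size cannot be estimated from the article. The illustrative false-positive rates for a pooled correlation, about 7% to about 40%, rest on assumed shifts between arms and on a pooling choice that the article does not state; the interaction rates rest on an assumed health factor. They show that the problem can be material, not that it will be.

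It would be wrong to conclude that the trial's efficacy result is compromised. The primary Timed-Up & Go analysis is an intervention-by-time comparison that does not use adherence. The consequence is confined to secondary and exploratory interpretation. The change is still worth making because it is cheap and prevents a misreading.

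**What to change.** - Make the abstract and Analysis of moderators agree, with baseline variables only. If expectation is kept, specify its T0 value and add it to the methods list.
- Remove adherence as a moderator, and do not offer an arm-by-adherence interaction as evidence on efficacy.
- In the sub-study analyses, state that the adherence-change association is reported separately within each arm, adjusted for the baseline value of the outcome and for frailty status. Label it exploratory and say that confounding by motivation and health remains.
- State that T0 to T1 dose is not pooled over arms, because the idle-time rule differs.

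The cost is a few sentences and a smaller n for an exploratory association: roughly 48 per arm of the 96 in the sub-study, or 36 after 25% dropout. Data collection does not change.

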**Discussion:**

This study will determine the efficacy, adherence and participants’ perception of a home-based multidomain intervention programme and its functionalities. This will allow for further development and possible commercialization of a scientifically validated training programme.

**Trial registration:**

ClinicalTrials.gov, NCT04237519 Registered on January 22, 2020 - Retrospectively registered.

## Background

Finding ways to improve and maintain functional abilities and quality of life in older adults has become a worldwide priority. It is well recognized that a reduced engagement in physical, cognitive and social activities has a negative influence on the health of older adults, exposing them to being more vulnerable both physically and cognitively. Sedentary behaviours can ultimately lead to physical frailty, which is defined as a state of high vulnerability with cumulation of adverse health outcomes [1, 2]. Fear of falling and/or unsteady gait is a common component of physical frailty and falls are particularly frequent in older adults [3, 4]. In addition to mobility limitation and falls, cognitive decline has been identified as a major cause of disability and dependency in older populations [5, 6].

Expert recommendations propose that non-pharmacological interventions focusing on modifiable lifestyle factors can be used to protect older people from the deleterious effects of physical and brain aging that can lead to disability [7, 8]. Keeping a healthy mind in a healthy body might be the approach of choice for healthy aging. Several studies have shown that physical activity induces many beneficial effects on general health, cognition and quality of life in healthy older adults but also in frail individuals [9–14]. In parallel to studies on physical activity, increasing evidence shows that cognitive training can also have a positive impact not only on cognition but also on physical status [15–23]. This is consistent with findings indicating that cognitive deficits, mainly impairment of executive functions and attentional control, are associated with falls [24] and abnormal gait [25].

Because aging is complex and different interventions are likely to potentiate their effects, an increasing number of studies have relied on combined interventions targeting two or more modifiable factors (for a review see [26]). For instance, the FINGER study, which combined face-to-face physical exercises and diet guidance with a home-based computerised-cognitive training, showed cognitive improvement on processing speed and executive functions [27]. The MAPT study used a multidomain intervention, which combined face-to-face cognitive training, diet and physical exercises guidance [28]. However, as these programmes were provided face-to-face for the most part, accessibility remains a potential barrier, as older adults may experience mobility challenges or may not have easy access to resources or facilities that can provide those programmes in their community or nearby environment.

Relying on computerisation to deliver lifestyle interventions has several advantages: it can be used to support home-based training, which reduces costs and increases access; training can be self-paced and repeated as wished; it helps provide immediate feedback; it allows scaling up for wider use if efficacy is proven; and it provides an excellent interface for active control interventions [29–31]. Surprisingly, whereas many studies assessed computerised cognitive training programmes, very few have combined at-home computerised cognitive and physical activity training [32–35]. Furthermore, few studies have integrated and assessed the user viewpoint. Adoption of technology by older adults depends on whether it responds to their needs and whether it is adapted to their capabilities [36, 37]. Barriers of technical nature (e.g., difficulty logging in or navigating) are often raised by older adults when measuring their interest for computerised brain health programmes [38]. This stresses the importance of collecting data on the perception of the programme and its functionalities and working with developers to adapt programmes to end users. This will be done in the present study by measuring usability, acceptability and user experience.

The StayFitLonger study was designed to test efficacy, adherence and perception of a home-based computerised training programme, which combines physical exercises and cognitive training in both robust and pre-frail older adults. The ultimate goal of the training programme is to maintain independent living at home by upholding and when possible improving physical and cognitive capacities in older adults. The programme comprises easily implemented videos of physical exercises focusing on gait and strength (Test-and-Exercise home-based programme, T&E, [39]). It also includes a series of ludic activities to increase cognitive functions. These cognitive activities train attentional control through dual-task exercises that were found to increase divided attention capacities and frontal lobe function [40], general knowledge learning and problem-solving capacities. Other features of the programme include: 1) prospective memory exercises embedded in the physical exercises; 2) social functionalities (i.e., creating and sharing learning material with peers; chatting with peers about topics of interest and sharing solutions to common real-life problems) to encourage social engagement, as it is positively related to health status and cognitive functions in older adults and helps counteract isolation [41, 42]; 3) psychoeducational content on cognition, physical health, nutrition and on ways to apply newly learned strategies in real life to empower participants and promote self-management (e.g., [43]); 4) a virtual coach to improve adherence by guiding participants, reminding them to use the programme regularly, and providing feedback and rewards through a system of virtual credits; 5) possibility to personalise the application settings to tailor the environment to the participant’s tastes and wishes (e.g. virtual coach apparence); and 6) wearable motion sensors, which are used during the physical exercises and one cognitive exercise in which a motor response is required, and as a complement to secondary outcomes.

## Objectives and hypotheses

The StayFitLonger study has two major objectives that will be addressed in the trial and the sub study. The **efficacy trial** will test the effect of the training on physical, cognitive, affective, and psychosocial outcomes using a 26-week double-blind parallel-group randomised control trial (RCT). Participants will be allocated randomly to either the StayFitLonger training home-based computerised programme (experimental intervention) or a home-based computerised comparator (active control). The primary objective is to assess whether the StayFitLonger programme leads to larger pre-post improvement than the active control condition on the Timed-Up & Go (TUG), a broadly used and validated functional physical task to measure lower extremity function, mobility and balance. Participants allocated to the experimental intervention are expected to show larger post-training improvement on the TUG than participants in the control intervention. As a secondary objective, we will assess whether the StayFitLonger programme improves physical, cognitive, affective, and psychosocial secondary outcomes. We will also explore whether gains differs in robust vs. pre-frail seniors since some studies suggest that changes in response to training might depend on frailty status [11, 14].

The **adherence sub-study** will rely on a pragmatic quasi-experimental design. At the end of the 26-week RCT, participants in the experimental group will be asked to continue using the programme and participants in the control group will ‘cross-over’ to the StayFitLonger programme. This sub-study will last 22 weeks and indicators of adherence will be recorded throughout the entire duration of the StayFitLonger study (48 weeks). This will allow us to assess whether adherence is maintained over time and whether it is influenced by personal characteristics, the presence or not of supervision and the type of intervention. Usability, acceptability and user experience will also be evaluated.

